### Intervention delivery

Both interventions will be delivered by iPlato: an mHealth company who have previous experience delivering text message reminders and PN for other cancer screening programmes (eg, breast) and are used for general services by over 90% of London’s general practices.^20^ The callers are experienced navigators who have previously delivered PN to breast cancer screening non-attenders. They regularly attend training, provided by Health Education England, and will have completed the following Health Education England programmes, before the study commences: (1) behaviour change literacy for individuals and workforce; (2) cancer in the community; (3) communicating with empathy (making the most of listening); (4) data security awareness; (5) population screening; (6) shared decision-making; (7) the changing story of cancer and (8) cultural competence. Calls will not be recorded.

To protect patient confidentiality, navigators will not leave messages (as these messages may be intercepted by others) or reveal the reason for their call to others. A dedicated telephone number will be set up for the study and will not be withheld from participants.

The official start date for the research was August 2021. However, due to disruptions to bowel cancer screening delivery (ie, temporary suspension of the programme, following the onset of the COVID-19 pandemic), the study was paused while the programme went through recovery (ie, addressed backlogs in screening invitations and follow-up colonoscopy of abnormal results). The study recommenced in September 2022, with a focus on obtaining the necessary ethical approvals for the research (eg, sponsor approval, NHS ethics). Having obtained the necessary approvals, the planned start date for recruitment is set for July 2024. The trial will run for approximately 8 weeks (1 July 2024–25 August 2024), with a follow-up period of 11 weeks (25 August 2024–9 September 2024) for kits to be returned, following the delivery of the final intervention.

In line with standard practice, iPlato will use a numerical score structure to assess participant satisfaction with the calls (see online supplemental appendix 3). An open question will also be administered, via text message, to obtain more detailed feedback/free-text responses. Responses will be reported using descriptive statistics to describe the means and distributions of the numerical structures. Free-text responses will be used to supplement the scores, to explore reasons for high and low satisfaction. The score structure will be administered via text message immediately after the call.

### Blinding and randomisation

This will be a single-blind RCT. The study investigators will not know which individuals have been assigned to the intervention or control groups, until the end of the trial, when all data have been collected and anonymised. Individuals registered at a participating GP practice will not be informed that they are participants in a study, during the study period; however, those receiving an intervention cannot be blinded to the condition they have been allocated, due to the overt nature of the interventions (hence, we describe this as a ‘single-blind’ RCT). Randomisation of individuals to study groups will be handled by iPlato, using simple, computerised, pseudorandom allocation methods. Individuals will be randomised in a 1:1:1 ratio to either the intervention or control condition, after 13 weeks of their screening episode, irrespective of whether or not they have a mobile number registered on their GP’s clinical system.

### Outcomes

The primary outcome will be participation in screening (defined as the return of a completed FIT kit within 24 weeks of dispatch (episodes ‘reopened’ between 13 and 24 weeks contribute towards uptake)) and will be compared between the three trial arms. The secondary outcome will be the kit result (defined as ‘normal’ or ‘abnormal’) and will also be compared between the three trial arms. This will allow us to determine whether the interventions have not only increased participation but increased participation of those with pathology, specifically.

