### Data collection

At the end of the study (‘week 24’), the London Bowel Cancer Screening Hub will extract the following data on study participants, from the available bowel cancer screening system: sex, age, index of multiple deprivation quintile (derived from the participant’s postcode), adequate completion (ie, ‘kit returned’ (yes/no)) and bowel cancer screening result (normal/abnormal). The data will then be anonymised and analysed by a data analyst at the London Hub.

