### Sample size calculation

For the control, text-message reminder and PN groups, we anticipate that 1.0%, 3.2% and 15.0% of participants (respectively) will complete a kit by week 24 (this is based on data provided by NHS England, as well as previous research conducted with the London BCSP) (Personal Communication). We subsequently designed our sample size calculation to provide sufficient power to allow us to test for the smallest possible difference, between any two groups, of 2.2 percentage points (ie, 1% in the control vs 3.2% in the text message reminder group). As three separate comparisons are planned for the main analysis (control vs text message reminders; control vs PN; text message reminders vs PN), we used an adjusted significance level (ie, 0.015) for our sample size calculation (as per the Bonferroni correction method, which takes into account inflation of the alpha statistic, caused by multiple comparisons), so as to maintain an overall 5% probability for any false positive result. To achieve 80% power at this level, our study requires 901 subjects per group (2703 recruits in total; see table 2 for details).

**Table 2 T2:** Sample size calculations

	P1	P2	Alpha*	Beta	n (per arm)	n (total)
Comparison 1						
No intervention† versusText-message reminders‡	0.0098	0.0318	0.015	0.2	901	2703
Comparison 2						
No intervention† versusText-message reminder+PN§	0.0098	0.1334	0.015	0.2	92	276
Comparison 3						
Text-message reminders versusText-message reminder+PN§	0.0318	0.1334	0.015	0.2	156	468

* An adjusted Alpha of 0.015 has been used to account for inflation of the statistic, resulting from multiple comparisons (ie, 0.05 / 3).

† Expected uptake based on 2019 data for FOBt/FIT, 13-24 weeks after invitation (PHE, personal communication).

‡ Expected uptake for text reminders based on the results of the service evaluation for the Southeast London breast screening service (iPlato, personal communication).

§ Expected uptake for text reminders and patient navigation based on the results of the service evaluation for the Southeast London breast screening service (iPlato, personal communication).

FITfaecal immunochemical test

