### Data analysis

Descriptive statistics (ie, frequencies and percentages) will be used to report the demographic characteristics, primary outcome and secondary outcome by study group. Differences between study groups, with respect to the primary outcome, will be assessed using univariate and multivariate logistic regression, before and after adjusting for demographic covariates. As there are three study groups, pairwise comparisons will be performed to test for differences between any two groups. These analyses will be performed on an intention-to treat basis and per-protocol basis so that both the ‘real-world’ impact and the ‘potential’ impact of the interventions can be assessed (not all individuals will have a valid mobile number recorded on the GP clinical system and so not all intervention participants will be able to receive the text message reminder and PN interventions). To conduct the per-protocol analyses, we will include individuals with a mobile telephone number stored on the clinical system for the control group, individuals who successfully received a text message reminder for the text message reminder group, and individuals who answered the phone in the PN group. We will also perform subgroup analyses, to explore the effectiveness of the interventions, by demographic characteristics, on an intention-to-treat and per-protocol basis. Finally, we will perform a cost-effectiveness analysis, to estimate the costs of the interventions per additional person screened. This will involve dividing the total cost of intervention, by the number of additional people screened in each intervention arm, over and above the number screened in the control arm.

All analyses will be performed by using SSPS statistics (V.27.0).

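### The secondary outcome (kit result, normal or abnormal) exists only for returned kits and has no stated denominator; on its natural reading it does not measure whether more people with pathology took part

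*Protocol article*

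**What the plan says.** The definition is in the Outcomes section of the protocol article: "The secondary outcome will be the kit result (defined as ‘normal’ or ‘abnormal’) and will also be compared between the three trial arms". The same section gives the purpose, which is to learn "whether the interventions have not only increased participation but increased participation of those with pathology, specifically", and says the comparison will settle this.

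The Data collection section lists, among the items to be extracted for study participants, "adequate completion (ie, ‘kit returned’ (yes/no)) and bowel cancer screening result (normal/abnormal".

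The Data analysis section has one sentence that covers the secondary outcome: "Descriptive statistics (ie, frequencies and percentages) will be used to report the demographic characteristics, primary outcome and secondary outcome by study group". Modelling is tied to the other outcome: "Differences between study groups, with respect to the primary outcome, will be assessed using univariate and multivariate logistic regression". The intention-to-treat and per-protocol statement follows from that modelling. No section says whether percentages for the kit result are taken over people randomised or over kits returned.

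**The concern.** The outcome has two levels and no place for a person who returns no kit. On the planned rates, that is roughly 87% to 99% of those randomised. Its natural percentage is therefore the share abnormal among returned kits. Returning a kit is the primary outcome, which the interventions are meant to change, so the returners in the three arms are no longer randomised groups. Each arm's returners have been selected by a different process.

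The question asked is whether participation by people with pathology went up. With an abnormal result as the marker, as the plan intends, that is a quantity per person randomised: how many people in each arm took part and had an abnormal result. The share among returners is a different quantity. It can stay flat while that number rises many-fold, and under some conditions it can fall. This is the protocol's only listed outcome bearing on clinical yield, so a misread result would matter to a programme deciding whether to adopt either intervention.

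**Working it through.** **Inputs from the protocol (Sample size calculation and Table 2).** Return by week 24: control 0.0098, text 0.0318, navigation 0.1334. The running text gives rounded or different values: "we anticipate that 1.0%, 3.2% and 15.0% of participants (respectively) will complete a kit by week 24". The planned size is 901 per arm. Positivity is not in the document; 2%, 5% and 10% are used below as assumptions.

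**Step 1: reproduce the plan's own figure.** The first row of Table 2 reads "0.0098 0.0318 0.015 0.2 901 2703". With a two-sided test, pooled variance under the null and no continuity correction:

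n = [z(1−α/2)·√(2·p̄·(1−p̄)) + z(0.80)·√(p1(1−p1) + p2(1−p2))]² / (p1−p2)²

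With p1 = 0.0098, p2 = 0.0318 and α = 0.015 this gives 901 per arm. The other two rows reproduce as 92 and 156. The rates and the 901 are therefore a sound base for what follows.

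**Step 2: expected kits with a result, per 901.**
- Control: 901 × 0.0098 = 8.8
- Text: 901 × 0.0318 = 28.7
- Navigation: 901 × 0.1334 = 120.2 (901 × 0.15 = 135 at the rate in the text)

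**Step 3: equal positivity in all arms.** Expected abnormal results = kits × positivity.

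| Assumed positivity | Control | Text | Navigation | Share among returners |
|---|---|---|---|---|
| 2% | 0.18 | 0.57 | 2.4 | 2% in every arm |
| 5% | 0.44 | 1.43 | 6.0 | 5% in every arm |
| 10% | 0.88 | 2.87 | 12.0 | 10% in every arm |

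Positivity cancels in the ratio of counts: navigation to control is 0.1334/0.0098 = 13.6, and text to control is 0.0318/0.0098 = 3.2. The share among returners shows none of this.

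**Step 4: unequal positivity.** Let r be positivity in the intervention arm divided by positivity in control. The intervention arm has more people with an abnormal result whenever r × (its return rate) exceeds 0.0098:
- Navigation: r > 0.0098/0.1334 = 7.3%
- Text: r > 0.0098/0.0318 = 31%

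For r between that bound and 100%, the share among returners is lower than in control while the number of people with abnormal results is higher. Illustration with assumed positivity of 10% in control and 4% in navigation: the share falls from 10% to 4%, yet abnormal results per person randomised rise from 0.0098 × 0.10 = 0.098% to 0.1334 × 0.04 = 0.534%. That is 0.9 against 4.8 people, or 5.4 times.

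**Step 5: how much information there is.** With about 9 control kits, the chance of no abnormal control result is (1 − positivity)^9 = 83%, 63% and 39% at 2%, 5% and 10%. Moving to all randomised does not make the trial large enough. With equal positivity and α = 0.05/3, approximate power for control against navigation is 16%, 42% and 76%; for control against text it is below 10% throughout. With expected counts this small, these normal-approximation figures are only rough.

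**The case against.** **The denominator is unstated, not wrong.** No sentence restricts the analysis to returners. Frequencies of abnormal results by study group, set beside the numbers randomised, would answer the question, and an article may leave such detail to a fuller document. The silence is real, and it is why the point is limited to the natural reading. But the article does state a two-level outcome that leaves non-returners out, and it attaches a firm inference to it. That goes beyond missing detail.

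**No test is planned.** Data analysis fixes only descriptive statistics for this outcome. This stands. A reader might infer that the trial is set to declare an effective intervention a failure. The document does not support that: it specifies no test or decision rule here, and the reported counts would show how few control kits there are.

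**The wording may ask about enrichment.** It could mean whether the extra participants are disproportionately people with pathology. Positivity among returners then bears on the question, with a caution about selection. Abnormal results per person randomised would not answer it, since they equal uptake times positivity and, at equal positivity, simply follow uptake. This reading is possible, so it would be too strong to say the outcome cannot answer any version of the question. Even so, about 9 control kits could not settle it.

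**The reversal rests on assumed inputs.** Correct. The protocol gives no positivity and no reason to expect it to be lower in an intervention arm. A reader might infer that reversal is likely; the document neither supports that nor rules it out. The failure at equal positivity does not depend on it.

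**Conclusion.** The point holds in limited form. As defined, the secondary outcome exists only for returned kits, has no denominator and, read naturally, conditions on the primary outcome. It then does not measure whether more people with pathology took part.

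Given the Table 2 rates, equal positivity is enough to show the problem: identical shares among returners beside about 13.6-fold (navigation) and 3.2-fold (text) differences in abnormal results. A result in the opposite direction is a possibility only, for positivity ratios of about 7% to 100% (navigation) and 31% to 100% (text). On either reading the data are too sparse for the certainty the Outcomes section expresses. At an assumed 2% to 10% positivity, control would yield about 0.2 to 0.9 abnormal results. The primary outcome and its analysis are not affected.

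**What to change.** In the Outcomes section, define the secondary outcome as an abnormal FIT result by week 24 (yes/no) among all people randomised, counting non-return as no abnormal result detected. In Data analysis, report by arm the count and the number randomised, with pairwise risk differences and exact or score confidence intervals, and make no significance claim.

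Keep positivity among returners as a descriptive figure for the enrichment question, with a note that returners are selected after randomisation. Replace the statement that the comparison will settle the matter with one that it will give an estimate.

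The cost is wording only: kit return and result are both already on the extraction list. The change should be recorded before anyone sees results by arm. The drawback is that the outcome must be reported openly as imprecise, because the trial is not sized for it.

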### Data collection

At the end of the study (‘week 24’), the London Bowel Cancer Screening Hub will extract the following data on study participants, from the available bowel cancer screening system: sex, age, index of multiple deprivation quintile (derived from the participant’s postcode), adequate completion (ie, ‘kit returned’ (yes/no)) and bowel cancer screening result (normal/abnormal). The data will then be anonymised and analysed by a data analyst at the London Hub.

### Sample size calculation

For the control, text-message reminder and PN groups, we anticipate that 1.0%, 3.2% and 15.0% of participants (respectively) will complete a kit by week 24 (this is based on data provided by NHS England, as well as previous research conducted with the London BCSP) (Personal Communication). We subsequently designed our sample size calculation to provide sufficient power to allow us to test for the smallest possible difference, between any two groups, of 2.2 percentage points (ie, 1% in the control vs 3.2% in the text message reminder group). As three separate comparisons are planned for the main analysis (control vs text message reminders; control vs PN; text message reminders vs PN), we used an adjusted significance level (ie, 0.015) for our sample size calculation (as per the Bonferroni correction method, which takes into account inflation of the alpha statistic, caused by multiple comparisons), so as to maintain an overall 5% probability for any false positive result. To achieve 80% power at this level, our study requires 901 subjects per group (2703 recruits in total; see table 2 for details).

**Table 2 T2:** Sample size calculations

	P1	P2	Alpha*	Beta	n (per arm)	n (total)
Comparison 1						
No intervention† versusText-message reminders‡	0.0098	0.0318	0.015	0.2	901	2703
Comparison 2						
No intervention† versusText-message reminder+PN§	0.0098	0.1334	0.015	0.2	92	276
Comparison 3						
Text-message reminders versusText-message reminder+PN§	0.0318	0.1334	0.015	0.2	156	468

* An adjusted Alpha of 0.015 has been used to account for inflation of the statistic, resulting from multiple comparisons (ie, 0.05 / 3).

† Expected uptake based on 2019 data for FOBt/FIT, 13-24 weeks after invitation (PHE, personal communication).

‡ Expected uptake for text reminders based on the results of the service evaluation for the Southeast London breast screening service (iPlato, personal communication).

§ Expected uptake for text reminders and patient navigation based on the results of the service evaluation for the Southeast London breast screening service (iPlato, personal communication).

FITfaecal immunochemical test

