**Methods and analysis:**

This study will use a three-arm randomised controlled trial design to compare the effectiveness and cost-effectiveness of text message reminders and PN to increase the uptake of bowel cancer screening in London. Participants will be individuals who have not returned a completed faecal immunochemical test kit within 13 weeks of receiving a routine invitation from the London bowel cancer screening hub. Participants will be randomised (in a 1:1:1 ratio) to receive either (1) usual care (ie, ‘no intervention’), (2) a text message reminder at 13 weeks, followed by repeated text message reminders at 15, 17 and 19 weeks (in the event of non-response) or (3) a text message reminder at 13 weeks, followed by PN telephone calls at 15, 17 and 19 weeks in the event of non-response. The primary endpoint will be participation in bowel cancer screening, defined as ‘the return of a completed kit by week 24’. Statistical analysis will use multivariate logistic regression and will incorporate pairwise comparisons of all three groups, adjusted for multiple testing.

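### Single-step Bonferroni, the only method named for the three pairwise contrasts, is valid but less efficient than the declared 5% error requires; a step-down rule would raise control-versus-text power from about 81% to 91% at the planned rates

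*Protocol article*

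**What the plan says.** The sample size section of the protocol article plans three contrasts ("control vs text message reminders; control vs PN; text message reminders vs PN"). It states that "we used an adjusted significance level (ie, 0.015) for our sample size calculation", and gives the purpose: "so as to maintain an overall 5% probability for any false positive result". The method is named once, "as per the Bonferroni correction method, which takes into account inflation of the alpha statistic, caused by multiple comparisons". The footnote to Table 2 derives the level as 0.05 divided by 3. On that basis, "To achieve 80% power at this level, our study requires 901 subjects per group".

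Table 2 shows that one contrast sets the size of the trial. Control versus text needs 901 per arm; the two contrasts with PN need 92 and 156.

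On the analysis itself the article says less. The abstract says that the regression "will incorporate pairwise comparisons of all three groups, adjusted for multiple testing". The data analysis section says that "pairwise comparisons will be performed to test for differences between any two groups" and names no procedure.

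**The concern.** Bonferroni treats the three null hypotheses as if any combination of them could be true. With three arms that is not so: if two of the equalities hold, so does the third. Once one pairwise null is false, at most one of the other two can be true. A procedure that uses this can test the remaining contrasts at a more generous level without exceeding the declared 5%.

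This matters most for control versus text. It is the only contrast with marginal power, and it decides whether the cheaper intervention is shown to work. The plan itself expects the two PN contrasts to be so large that they reject almost with certainty, which is when a step-down rule helps most.

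**Working it through.** **Inputs** (Table 2): control 0.0098, text 0.0318, text plus PN 0.1334; alpha 0.015; power 80%; allocation 1:1:1. Two-sided tests are inferred, because the two-sided formula returns all three of the plan's numbers and the one-sided formula gives 763 for the first.

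**1. Reproduce the plan.** With p̄ = (p1 + p2)/2, the pooled formula is

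n = [z(1−α/2)·√(2p̄(1−p̄)) + z(0.80)·√(p1(1−p1) + p2(1−p2))]² / (p1−p2)².

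For control versus text, p̄ = 0.0208 and z(1−0.015/2) = 2.4324, so n = (0.4909 + 0.1694)²/0.022² = 900.8, that is 901. The other two contrasts give 92 and 156. All three match. At exactly 0.05/3 the first would be 880.

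**2. Power for control versus text at 901 per arm.** The standard error is 0.006724 under the null and 0.006704 under the alternative. Power = Φ[(0.022 − z·0.006724)/0.006704].

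| Level | z | Power |
|---|---|---|
| 0.015 | 2.432 | 80.0% |
| 0.05/3 | 2.394 | 81.1% |
| 0.05 | 1.960 | 90.6% |

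Both PN contrasts have power above 99.99% even at 0.015. At the planned rates a step-down rule therefore tests control versus text at 0.05 in practically every trial. About 1 point of the rise from 80.0% to 90.6% only undoes writing 0.05/3 as 0.015; the other 9.5 points come from the step-down.

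**3. Family-wise error of Shaffer's rule** (smallest p at 0.05/3; if it rejects, the other two at 0.05).
- All three nulls true: any false rejection needs the smallest p at or below 0.05/3, with probability at most 3 × 0.05/3 = 0.05.
- Exactly one null true: a false rejection needs that p at or below 0.05, with probability at most 0.05.
- Exactly two nulls true: impossible with three arms.

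The same logic holds for the three contrasts of one treatment factor in a single logistic model. Simulation with unadjusted pooled z-tests (400,000 replicates) agrees: 3.8% with all arms at 0.98%, 4.4% with all at 3.18%, and no more than 5.0% with one true null pair.

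**4. Dependence on the PN rate.** Simulated power for control versus text, 901 per arm:

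| PN rate | Bonferroni 0.015 | Bonferroni 0.05/3 | Holm | Shaffer |
|---|---|---|---|---|
| 13.34% (planned) | 82% | 83% | 93% | 93% |
| 5% | 82% | 83% | 91% | 92% |
| 3.18% (equal to text) | 82% | 83% | 86% | 90% |
| 2% | 82% | 83% | 84% | 85% |

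Simulated values lie about 2 points above the formula, because the normal approximation is rough with about 9 expected events in the control arm (901 × 0.0098 = 8.8). The difference between methods at the planned rate is much the same either way.

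**5. Error on control versus text alone.** With 0.98% / 0.98% / 13.34% (PN works, text does nothing), a false claim for text occurs in about 1.3% of simulated trials at 0.015, 1.4% at 0.05/3, and 4.9% under Holm or Shaffer.

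**The case against.** The strongest reply is that nothing here is wrong. Bonferroni controls the error whatever the dependence between tests, the trial reaches its stated 80% on its weakest contrast, and a preference for a sharper method is only a preference. It stands that the plan contains no validity error. It does not remove the point: against Bonferroni at 0.05/3, the step-down rule rejects everything that Bonferroni rejects, within the same declared 5% and with no extra participants.

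Second, a reader might infer that the analysis is bound to test at 0.015 and so throws power away. The text does not establish that. The sample size section ties 0.015 to the calculation of N, and the abstract and data analysis section leave the adjustment open. A step-down analysis would fit the wording as it is. The accurate statement is that single-step Bonferroni is the only method named.

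Third, a reader might infer that the extra strictness buys nothing. It does buy something: when PN works and text does not, it keeps the error on control versus text near 1.4% instead of 4.9%. A team that wants tight control on that single contrast, or simultaneous intervals that match its tests, could choose Bonferroni on purpose. The article, however, declares only the overall 5% as its aim.

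Fourth, the gain is not guaranteed. The PN rate comes from a breast screening service evaluation, and Holm and Shaffer differ away from the planned rates. Both remarks are right, and the table above reflects them.

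Finally, the simulations use unadjusted z-tests and a limited set of null configurations, while the plan uses logistic regression. The error bound in step 3 needs only valid pairwise p-values, but the exact power figures are approximations.

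**Conclusion.** The point holds as one of efficiency. At 901 per arm and the Table 2 rates, Shaffer's or Holm's procedure gives 90.6% power for control versus text by the normal approximation, against 81.1% with Bonferroni at 0.05/3 and 80.0% at the 0.015 used. The family-wise error stays at or below 5%. These figures assume two-sided tests, the planned PN rate and no loss of outcome data. If PN only equals text, simulated power is about 90% (Shaffer) or 86% (Holm) against 83% for Bonferroni at 0.05/3. If PN reaches 2%, it is about 85% or 84%. The documents do not support reading this as an inflated error rate, an underpowered design or a wrong sample size.

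**What to change.** In the data analysis section, state before outcome data are seen that the three pairwise p-values from the primary model will be tested by Shaffer's step-down procedure: smallest at 0.05/3; if it rejects, the other two at 0.05. Adjusted p-values are then three times the smallest p (at most 1) and, for each of the others, the larger of its own p and that value. Holm's procedure is an acceptable alternative with a smaller gain if PN disappoints.

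Keep 901 per arm and treat the extra power as reserve. Randomisation ignores whether a mobile number is held, so some of the effect may be lost under intention-to-treat. The article gives no figure for this. As an assumption, if 10% or 20% of the 2.2-point difference were lost (text rate 0.0296 or 0.0274), the formula in step 2 gives 72% or 63% power at 0.015, and 86% or 79% at 0.05.

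The cost is a sentence or two of text and two acknowledged downsides. The error on control versus text alone can rise to about 5%, still within the declared total. Simple simultaneous intervals no longer match the tests, so report unadjusted 95% intervals, labelled as such, beside the adjusted p-values.

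### The adjusted significance level is given as 0.015 and derived as 0.05/3, but 0.05/3 is 0.0167; the slip is conservative, and the level should be reconciled

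*Protocol article*

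**What the plan says.** All the relevant statements are in the protocol article, under Sample size calculation.

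- The reason for adjusting: "As three separate comparisons are planned for the main analysis" (control versus text message, control versus patient navigation, text message versus patient navigation).
- The level: "we used an adjusted significance level (ie, 0.015) for our sample size calculation", described "as per the Bonferroni correction method", with the purpose "so as to maintain an overall 5% probability for any false positive result".
- The resulting size: "To achieve 80% power at this level, our study requires 901 subjects per group (2703 recruits in total").
- Table 2 prints alpha 0.015 in all three rows. The row that sets the trial's size reads "0.0098 0.0318 0.015 0.2 901 2703" (P1, P2, alpha, beta, n per arm, n total).
- The table footnote gives the origin of the level: "An adjusted Alpha of 0.015 has been used to account for inflation of the statistic, resulting from multiple comparisons (ie, 0.05 / 3").

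The abstract says that the pairwise comparisons will be adjusted for multiple testing. The Data analysis section describes the pairwise comparisons but gives no numerical threshold.

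**The concern.** The footnote equates two different numbers. Bonferroni for three comparisons at an overall 5% gives 0.05/3 = 0.01667. That is 0.017 to three decimals, 0.02 to two, and 0.016 if truncated after three. None of these is 0.015.

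Two things follow. First, if 0.015 went into the calculation, the trial's headline size rests on a level other than the one its own derivation gives. Second, this is the only place in the article with a numerical per-comparison level, and it supports two readings. A primary contrast with p between 0.015 and 0.0167 would be significant under one and not under the other. A multiplicity rule fixed in advance should leave no such choice once the results are known.

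**Working it through.** **Inputs (Sample size calculation and Table 2).** Anticipated uptake 0.0098 (control), 0.0318 (text message) and 0.1334 (text message plus navigation); alpha 0.015; beta 0.2; equal allocation. Sidedness is not stated. Two-sided is inferred because it reproduces all three printed sizes.

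**Formula.** Normal approximation with pooled variance under the null and no continuity correction, where p̄ = (p1 + p2)/2:

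n per arm = [ z(1−α/2) · √(2p̄(1−p̄)) + z(0.80) · √(p1(1−p1) + p2(1−p2)) ]² / (p2 − p1)²

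**Step 1: reproduce the plan at 0.015.** z(1−0.0075) = 2.4324 and z(0.80) = 0.8416. For control versus text message, p̄ = 0.0208, the two square roots are 0.20183 and 0.20123, and the difference is 0.0220:

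n = (2.4324 × 0.20183 + 0.8416 × 0.20123)² / 0.0220² = (0.49092 + 0.16936)² / 0.000484 = 900.8, so 901.

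The other two comparisons give 91.9 (92) and 156.0 (156). All three printed sizes are matched exactly. At 0.015, other common variants do not match:

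| Variant at 0.015 | n per arm |
|---|---|
| One-sided, pooled | 763 / 78 / 132 |
| Two-sided with continuity correction | 990 / 108 / 176 |
| Two-sided, unpooled | 897 / 88 / 153 |
| Two-sided, arcsine | 835 / 72 / 142 |

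So 0.015 is the value that entered the calculation, not a display rounding of 0.0167.

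**Step 2: the same formula at 0.05/3.** z(1−0.00833) = 2.3940. For control versus text message:

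n = (2.3940 × 0.20183 + 0.16936)² / 0.000484 = (0.48317 + 0.16936)² / 0.000484 = 879.7, so 880.

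| Comparison | n per arm at 0.015 | n per arm at 0.05/3 |
|---|---|---|
| Control vs text message | 901 | 880 |
| Control vs text message + navigation | 92 | 90 |
| Text message vs text message + navigation | 156 | 153 |

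The largest requirement sets the trial: 3 × 880 = 2640 against 3 × 901 = 2703, which is 63 fewer (63/2703 = 2.3%).

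**Step 3: power with 901 per arm.** Power = Φ{ [ (p2 − p1)√n − z(1−α/2)√(2p̄(1−p̄)) ] / √(p1(1−p1) + p2(1−p2)) }. For control versus text message, (p2 − p1)√n = 0.0220 × √901 = 0.66037.

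- At 0.015: (0.66037 − 0.49092)/0.20123 = 0.842, power 80.0%.
- At 0.05/3: (0.66037 − 0.48317)/0.20123 = 0.881, power 81.1%.

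The other two comparisons exceed 99.9% with 901 per arm at either level.

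**Step 4: familywise error.** The Bonferroni bound is 3 × 0.015 = 0.045 at the printed level and 3 × 0.05/3 = 0.05 at the derived one. Both respect the 5% limit.

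**The case against.** The strongest reply is that nothing built on 0.015 is wrong. The text claims 80% power at that level, every row of Table 2 prints it, and the sizes reproduce exactly. A reader might infer from the false equation that the sample sizes or the power are misstated. The documents do not support that: 901, 92, 156 and 80% are correct for the inputs printed beside them, and 81.1% is the power at a level that the calculation did not use. Nor is the 5% aim breached, since a bound of 4.5% lies inside it. This part of the reply stands.

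A reader might also infer that 0.015 is the analysis threshold, so that some results would be wrongly declared non-significant. That too goes beyond the text. The article ties 0.015 to the sample size calculation, the Data analysis section sets no number, and a full protocol or analysis plan that is not shown may state the threshold. Any effect on conclusions is therefore conditional.

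The reply does not remove the equation itself. The text names Bonferroni for three comparisons, the footnote writes out the division, and the result given is not the result of that division. A threshold stated elsewhere would not correct that. It is also fair to say that 0.015 is a legitimate level under a 5% familywise limit. But the article presents it as the outcome of 0.05/3, not as a deliberate stricter choice.

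**Conclusion.** The concern holds as a minor internal contradiction. The level used (0.015) is not the level its stated derivation gives (0.0167), and the printed sizes follow the former. The error is on the safe side: the familywise bound is 4.5%, power for the sizing comparison is at least 80% under either level, and the trial is 21 per arm larger than 0.05/3 would require. It is neither underpowered nor anti-conservative on this account. The remaining exposure is a primary contrast with p between 0.015 and 0.0167, if 0.015 is taken as the analysis threshold. The comparison most exposed is control versus text message, the one sized at 80% power.

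These figures rest on the Table 2 uptake rates and on a two-sided pooled-variance calculation, inferred from its exact match to the printed sizes.

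**What to change.** Settle the level before outcome data are analysed, in one of two ways.

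1. State 0.05/3 (0.0167) as the per-comparison level for the three pairwise tests, in the text and in Table 2. Keep 901 per arm (2703 in total), restate power for control versus text message as about 81%, and give the Table 2 requirements at that level as 880, 90 and 153.
2. Keep 0.015 with the existing sizes and 80% power. Delete the 0.05/3 derivation, describe 0.015 as a deliberately stricter level with a 4.5% familywise bound, and say that it governs the analysis.

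Either way, state the chosen threshold once in the Data analysis section, so that the sizing and the tests use the same number. Enrolment need not be cut. The cost is a correction to the text and one table.
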